## Background

Dengue is a major threat to global public health, with an estimated annual incidence of 390 million infections worldwide, leading to approximately 96 million symptomatic cases and 22,000 deaths in more than 120 countries
^1^. Despite increasing understanding of dengue pathogenesis, effective anti-viral or disease modifying agents are yet to be identified, and patient management remains reliant on judicious fluid replacement in response to plasma leakage during the critical phase of illness (usually days 4–6)
^2,
3^.

While the vast majority of symptomatic infections give rise to the milder form of disease, dengue fever, those that progress to severe disease carry significant risk of vital organ dysfunction and death. Several patient groups have been identified as being at particular risk of severe dengue, including the elderly, pregnant women, those with comorbid illness, and those with prior exposure to alternative dengue serotypes
^4^. An important and increasingly recognised severe dengue risk factor is obesity, a condition which has had a dramatic increase in prevalence among Vietnamese children and adolescents over the last two decades
^5^. Several observational studies have reported an association between obesity and severe dengue
^6–
9^. A recent systematic review and meta-analysis reported the odds of developing severe dengue to be significantly higher in obese children in comparison to their non-obese counterparts (OR = 1.38; 95%CI 1.10 - 1.73)
^10^.

The underlying mechanism remains unknown, but could possibly be explained by chronic low-grade inflammation that is induced by being overweight or obese
^11,
12^. Adipocytes are known to produce pro-inflammatory cytokines and adipokines, such as adiponectin, resistin and leptin, each of which have a role in immunomodulation. Obesity-induced leptin and resistin are known to be associated with many of the physiological abnormalities seen in dengue, including platelet dysfunction, vascular inflammation, myocardial injury, endothelial dysfunction
^13–
16^, and capillary hyper-permeability
^17–
19^. Additionally, it is possible that more severe infection is permitted by altered CD8
^+^ T cell immunity and impairment of natural killer (NK) cell activity in obese hosts
^20,
21^.

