**Figure 1. f1:**
[figure not shown]
Trial flow chart.

The 60 patients receiving treatment will be compared to 60 overweight or obese patients with standard of care (without treatment) recruited contemporaneously from the same wards, with the same enrolment criteria, in an ongoing observational study as the control arm.

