### Inclusion and exclusion criteria

Patients will be eligible for study enrolment if they: (i) are aged between 10 and 30 years; (ii) have a clinical diagnosis of dengue (based on World Health Organization (WHO) – Dengue guidelines)
^2^; (iii) are NS1 rapid antigen test positive; (iv) have BMI >25kg/m
^2^ (or BMI-for-age >1 SD); (v) are admitted within 72 hours of fever onset; (vi) agree to come back for FU visit between days 21–28 of illness; and (vii) provide written informed consent.

Exclusion criteria include: (i) pregnancy (confirmed by either clinical examination or urine dipstick for human chorionic gonadotrophin hormone); (ii) localising features suggestive of an alternative diagnosis; (iii) significant diarrhoea and/or vomiting (>3 episodes/24 hours); (iv) history of hypersensitivity to metformin; (v) current use of metformin or any other regular hypoglycaemic agent, including insulin; (vi) current use of any drug with significant metformin interaction (
*Extended data*
^46^); (vii) current treatment for heart failure or recent history of myocardial infarction (in the last year); (viii) presence of severe infection at enrolment, including severe dengue, central nervous system infection or septicaemia; (ix) baseline lactate level >2.0 mmol/L; (x) baseline blood glucose level <3.9 mmol/l (or <70 mg/dL); (xi) baseline liver impairment (alanine transaminase (ALT) and/or aspartate transaminase (AST) >250 U/L); and (xii) chronic renal impairment (glomerular filtration rate (GFR) <30 mL/min). Patients that are deemed unlikely to attend FU at 28 days from fever onset because of long travelling distance to the clinic will also be excluded.

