### Secondary endpoints

The secondary endpoints are: fever clearance time (the time from enrolment to sustained body temperature <37.5°C for 48 hours); platelet nadir and highest AST/ALT between days 3 and 8 of illness; percentage increase in haematocrit (HCT) from baseline (using HCT obtained at the 28 day FU visit to reflect baseline); plasma viraemia (area under the log
_10_-transformed viraemia curve from study days 3 to 6); time from enrolment to first undetectable viraemia and first negative NS1 measurement; trend over time (5 days) in VCAM1, CRP, leptin, adiponectin, low density lipoprotein (LDL), and AMPK phosphorylation; and magnitude of activated/proliferating T and NK cells as well as frequency and phenotype of dengue-specific CD4+ and CD8+ T cells, quantified by flow cytometry at enrolment and hospital discharge.

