### Statistical considerations

***Sample size.*** This is an exploratory study focusing primarily on safety, and there are no preliminary data regarding the effects of metformin in dengue on which to base a sample size calculation. A target sample size of 60 patients was chosen based on clinical judgement and feasibility considerations. Using the trend in VCAM over time, which is one of the secondary endpoints, by assuming a slope of change in concentration over time at 0.34 (log
_2_VCAM concentration per day, data based on biomarkers of endothelial function in dengue), we conducted a power calculation using a t-test to compare effects on endothelial function between two groups. It is suggested this study will have a power of 80% to detect a difference of at least 0.023 (log
_2_VCAM concentration per day) in the slope of change.

***Statistical analysis.*** The primary analysis population will include all patients from cohort 1 and cohort 2, plus 60 controls as mentioned previously. Baseline characteristics and outcomes will be summarised for each treatment group. The cohort of patients enrolled in this study will form the active treatment group, while the control group will consist of overweight and obese dengue patients that participated in a matched cohort observational study, none of whom received metformin therapy. Continuous variables will be described using medians and quartiles, while categorical variables will be described in terms of frequencies and percentages.

The primary endpoint (number of AEs), will be compared between the treatment groups using negative binomial regression model. The clinical, biomarker, immunological will be compared between the treatment arms using linear regression or random effects model for continuous endpoints, and Cox regression for time-to-event endpoints (fever clearance time, time to first undetectable viremia measurement, time to first negative NS1 measurement). All comparisons will be adjusted for age, sex, and day of illness, as patients will not be randomized. For percentage increase in HCT and area under the curve of viraemia, comparisons will be also adjusted for the pre-dose value of the respective marker.

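### The haematocrit comparison appears to adjust for raw pre-dose HCT although the outcome is relative to the patient's own day-28 HCT, so baseline haemoconcentration is only partly adjusted for

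*Protocol article*

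**What the plan says.** The Secondary endpoints section defines the outcome as "percentage increase in haematocrit (HCT) from baseline (using HCT obtained at the 28 day FU visit to reflect baseline"). Each patient's rise is thus expressed relative to that patient's own convalescent level.

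The Statistical analysis paragraph under Statistical considerations names "linear regression or random effects model for continuous endpoints" and states that "All comparisons will be adjusted for age, sex, and day of illness, as patients will not be randomized". It then adds one covariate for two endpoints, this one and the viraemia area under the curve, for which "comparisons will be also adjusted for the pre-dose value of the respective marker".

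No section defines a pre-dose percentage increase, and day-28 HCT is not named as a covariate. The protocol article gives no SD, coefficient of variation or correlation for HCT.

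**The concern.** Outcome and covariate appear to be on different scales. Take two patients, both with a pre-dose HCT of 45%. If the first has a day-28 HCT of 45%, he starts with 100 × (45 − 45)/45 = 0% haemoconcentration. If the second has a day-28 HCT of 38%, he starts at 100 × (45 − 38)/38 = 18%. Raw pre-dose HCT gives them the same covariate value, although they start far apart on the outcome's scale.

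Variation between patients in usual HCT therefore acts as noise in the covariate. It flattens the slope, and the model under-corrects for haemoconcentration present before the first dose. This matters because the arms are not randomised. HCT rise is also the only listed secondary endpoint that measures haemoconcentration, and the Discussion says that improvement in any secondary endpoint, with safety established, would justify a larger randomised trial.

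**Working it through.** The plan states no figure for this comparison, so there is nothing to reproduce. The check asks how much of a pre-dose arm difference survives each adjustment.

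**Inputs from the protocol.** The outcome, covariates and model are as quoted above. The design is described thus: "The 60 patients receiving treatment will be compared to 60 overweight or obese patients with standard of care (without treatment) recruited contemporaneously". On timing, patients qualify if they "are admitted within 72 hours of fever onset", and the Background places "plasma leakage during the critical phase of illness (usually days 4–6").

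**Assumed inputs (all in percent; none is in the protocol).** s_B is the SD of usual HCT after age and sex, s_L the SD of pre-dose haemoconcentration within arm, s_e the reading error, and c the fraction of pre-dose haemoconcentration that carries into the peak.

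**Model on the log-percent scale.** Pre-dose = B + L + e₀; peak = B + cL + later rise + e₁; day 28 = B + e₂; outcome Y = peak − day 28. With no true treatment effect, the share of an arm difference in L left in the treatment estimate is:

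- raw pre-dose HCT as covariate: c × (1 − λ), with λ = s_L² / (s_L² + s_B² + s_e²);
- pre-dose minus day 28 as covariate: (2c − 1) × k, with k = s_e² / (s_L² + 2s_e²).

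**Two worked cases, s_e = 2, arm difference 2 points.**

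- Case A, s_B = 7, s_L = 5: λ = 25/78 = 0.321, so 1 − λ = 0.679; k = 4/33 = 0.121.
- Case B, s_B = 5, s_L = 3: λ = 9/38 = 0.237, so 1 − λ = 0.763; k = 4/17 = 0.235.

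| Carry-forward c | A, raw | A, same scale | B, raw | B, same scale |
|---|---|---|---|---|
| 1 | 1.36 | 0.24 | 1.53 | 0.47 |
| 0.5 | 0.68 | 0 | 0.76 | 0 |
| 0.25 | 0.34 | −0.12 | 0.38 | −0.24 |
| 0 | 0 | −0.24 | 0 | −0.47 |

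Entries are points of bias. Simulation of 3000 trials of 60 v 60, later-rise SD 5%, c = 1, gave 1.36 and 0.24 for case A and 1.52 and 0.47 for case B, in agreement. Over s_B 5–9 and s_L 3–5 in that set-up, the variance of the treatment estimate was roughly 17–36% lower with the same-scale covariate.

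**Wider range.** A large-sample regression used the percentage outcome itself, adjusted for sex, with c = 1 and reading error 1.5%. It covered 30 combinations of s_B 4–8% and s_L 2–8%. The share of the pre-dose difference left was:

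- no HCT covariate: about 100%;
- raw pre-dose HCT: 25–94%, above 50% in 23 of the 30 combinations; for s_L of 2–4%, 55–94%;
- pre-dose percentage above day 28: 3–26%;
- raw pre-dose HCT together with day-28 HCT: 4–28%.

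Reading error changes what the fix can achieve. In three further combinations, an error of zero gave 44–82% with raw HCT and about 0% with either fix; an error of 3% gave 51–85% with raw HCT and 16–36% with the fixes.

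**The case against.** **The covariate may already be the right one.** The text says only the respective marker. Since the sentence begins with percentage increase in HCT, that could mean the pre-dose percentage increase, in which case the problem largely disappears. A reader might infer that the protocol states raw HCT outright; it does not. Raw HCT is still the more natural reading: the same sentence covers viraemia, where the marker is the measured quantity and not its area under the curve. On either reading the sentence needs the same clarification.

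**Most of the difference need not survive.** A reader might infer that most of any pre-dose difference is bound to be reported as a metformin effect. The documents do not support that. In 7 of the 30 combinations less than half remained, for example 44% with s_B 4% and s_L 5%. The percentages also assume full carry-forward into the peak, which the protocol neither states nor excludes. At c = 0.5 the raw-HCT bias halves.

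**The covariate is not the only safeguard.** A reader might infer that nothing else protects this comparison. The plan also adjusts for age, sex and day of illness. It uses the same criteria, wards and season for both groups, recruits in alternating two-week blocks and excludes severe dengue at enrolment. The pre-dose sample mostly precedes the usual leakage phase. This limits how large an imbalance can be, and the protocol gives no reason to expect any particular size. However, early sampling also implies a small s_L, which is where raw HCT is the weakest proxy. Day of illness handles differences in timing, not differences in leakage on the same day of illness.

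**The fix has a cost.** Day-28 reading error then enters both outcome and covariate, and the covariate uses a value taken after treatment. With no carry-forward this creates a bias of about −0.2 to −0.5 points for a 2-point imbalance, where raw HCT has none. This stands, but it is small. Setting the two absolute biases equal gives c = k / (1 − λ + 2k), which is 0.121/0.922 = 0.13 in case A and 0.235/1.234 = 0.19 in case B. Above that level of carry-forward the same-scale covariate is less biased. The day-28 value is already the outcome's denominator, so the plan already relies on it as a baseline.

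**Conclusion.** The point holds as one of incomplete adjustment. On the natural reading, the covariate for percentage increase in HCT is on a different scale from the outcome. It therefore removes only part of any arm difference in pre-dose haemoconcentration that remains after age, sex and day of illness. How large that part is cannot be known from the protocol. It is probably substantial if early haemoconcentration mostly persists into the peak, because s_L is plausibly small at enrolment, and it is smaller with less carry-forward. All sizes rest on assumed SDs, reading error and carry-forward, and the amount of imbalance itself is unknown.

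This concerns one secondary endpoint of an exploratory study whose primary focus is safety. It is a cheap improvement and no threat to the trial's main conclusion.

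**What to change.** In the Statistical analysis paragraph, state for percentage increase in HCT that the extra covariate is the pre-dose percentage above day-28 HCT, 100 × (pre-dose HCT − day-28 HCT) / day-28 HCT. Including day-28 HCT together with pre-dose HCT does about as well. On the log scale, the equivalent is to regress log(peak/day-28) on arm, age, sex, day of illness and log(pre-dose/day-28). Keep the raw-HCT model as a sensitivity analysis, because of the shared day-28 reading error. Leave the viraemia adjustment unchanged.

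The cost is one line of wording. Both HCT values are already needed, one for the outcome and one for the present adjustment, so no new data are collected. A patient without a day-28 HCT has no outcome in any case, so no further patients are lost.

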## Ethical considerations

### Ethical approval

The protocol, informed consent forms, assent forms and patient information sheets have been reviewed and approved by the ECs of the Hospital for Tropical Diseases in Ho Chi Minh City (CS/BND/19/34), the Vietnamese Ministry of Health (24/CN-HÐÐÐ) and the Oxford Tropical Research Ethics Committee (OxTREC reference: 36-19). The Investigator will submit and, where necessary, obtain approval from the above committees for all amendments to the originally approved documents.

### Informed consent and information sheet

All patients entering the study must give written informed consent. The study physician will describe the purpose of the study, the study procedures, possible risks/benefits, the rights and responsibilities of participants, and alternatives to enrolment. The patient or parent/guardian will be invited to ask questions which will be answered by study staff, and they will be provided with appropriate numbers to contact if they have any questions subsequently. If the patient or parent/guardian agrees to participate, they will be asked to sign informed consent/assent forms (ICFs;
*Extended data*
^46^). A copy of the form, with signature, will be given to them to keep. In addition to the procedures above, illiterate signatories will have the ICF read to them in the presence of a witness who will sign to confirm this.

Patients, who are between 10 and 18 years of age, will be asked to sign the assent form in which, the study purpose and procedures will be explained to them in child friendly terms. Their parent/guardian will be asked to sign the consent form as well to give permission for their child to participate in the study.

### Confidentiality

Patients who enter the trial will be given a unique identification number. This number will be used on both laboratory specimens and CRFs. The study wards and the research unit have the facilities to store study information securely. Only study staff will have access to the password-protected computer where entered data is stored. After conclusion of the study, data will be stored in a safe place. Any scientific publications or reports will not identify any patient by name or initials. When the research team reviews the clinical notes, they are also bound by professional confidentiality.

### Data monitoring and trial steering committees

A Trial Steering Committee (TSC) will be formed to provide overall supervision of the conduct of the trial and provide advice through its independent Chair. The ultimate decision for the continuation of the trial lies with the TSC. In particular, the TSC will concentrate on progress of the trial, adherence to the protocol, patient safety, and the consideration of new information.

An independent DMC will be set up consisting of qualified volunteers with the necessary knowledge of clinical trials and statistics. The DMC will review the protocol and agree to a data review schedule and reporting requirements before the study commences. All data reviewed by the DMC will be in the strictest confidence. A DMC charter will outline its responsibilities and operations (
*Extended data*
^46^).

Monitoring will then be carried out approximately annually by OUCRU CTU staff. The frequency, type and intensity of routine monitoring and the requirements for triggered monitoring will be detailed in the monitoring plan, which will also detail the procedures for review and sign-off. The monitoring will adhere to the principles of ICH GCP and the monitoring plan.

### Data collection and management

All study data will be recorded on standard CRFs and entered on the CliRes database. The participants will be identified by a unique study specific number and/or code in any database. The name and any other identifying detail will not be included in any stored electronic CRFs. Direct access will be granted to authorized representatives from the University of Oxford and any host institution for monitoring and/or audit of the study to ensure compliance with regulations. Original paper documents will be stored at the OUCRU-CTU for 15 years after which paper files will be scanned and archived electronically. Electronic data will be stored indefinitely on a secure OUCRU-VN server for a minimum period of 10 years and paper copies will be destroyed securely.

## Spirit checklist

A SPIRIT checklist for this trial protocol is attached (
*Reporting guidelines*
^46^).

## Data sharing and dissemination

In line with research transparency and greater access to data from trials, OUCRU’s clinical trials are registered at ClinicalTrials.gov and a data sharing policy is in place. Data exchange complies with Information Governance and Data Security policies in all of the relevant countries.

Participants will not be individually informed of results. Data from this study will be published in peer-reviewed journals. Authorship and reporting of this work will follow international guidelines and all authors will have made a noteworthy contribution to the work.

## Trial status

We expect that this trial will start recruiting patients in June 2020.

## Discussion

Despite increasing investment in strategies to prevent infection, dengue remains a major global pathogen, with extremely high associated health, social and economic disease burden
^47^. Severe dengue can be rapidly life threatening as a result of plasma leakage, hypovolaemic shock and subsequent end organ damage, and is known to disproportionately affect overweight and obese individuals. Although optimal supportive care is largely successful in permitting recovery from most dengue infections, effective therapeutic agents are desperately needed to enable treatment of patients with the greatest disease severity. Metformin has previously demonstrated therapeutic potential due to observed anti-viral and immunomodulatory effects, and an association with reduced risk of severe dengue in adults with T2DM. Additionally, its low cost and excellent safety profile in the treatment of T2DM make metformin a prime candidate for use in appropriately selected patients on a mass scale. This study will assess the safety and tolerability of metformin in the context of dengue infection, and whether metformin treatment early in the course of disease is clinically beneficial for overweight and obese children and young adults. It will also provide a key insight into the effects of metformin on markers of viral replication, endothelial dysfunction and the host immune response in this patient group. If the safety of this drug is established and this pilot study demonstrates improvement in any of the secondary endpoints, a larger randomized-controlled trial of metformin in dengue would be warranted

## Data availability

### Underlying data

No underlying data are associated with this article.

### Extended data

Oxford University Research Archive: Oxford University Clinical Research Unit Metformin trial supporting documents,
https://doi.org/10.5287/bodleian:5Rk2p9EVK
^46^.

- Consent form- Participant information sheet- DMC charter- Case Report Form- Drug interactions

### Reporting guidelines

Oxford University Research Archive: SPIRIT checklist for ‘Metformin as adjunctive therapy for dengue in overweight and obese patients: a protocol for an open-label clinical trial (MeDO)’,
https://doi.org/10.5287/bodleian:5Rk2p9EVK
^46^.

Data are available under the terms of the
Creative Commons Attribution 4.0 International license (CC-BY 4.0).
